#### Secondary outcomes

These will include the number of VM attempts used, evidence of postural modification, cardioversion (return to normal heart rhythm) as recorded by the treating ambulance clinician (including spontaneous cardioversion), total time of the ambulance episode and further ambulance attendances for SVT including subsequent conveyance to hospital (to rule out the possibility that treatment postpones attendance to hospital) during the 3-month period after the index presentation. Other outcome measures will include an estimate of diagnostic appropriateness (through the retrospective expert reading of available, interpretable pre-Valsalva ECG traces recorded in the ePCR) and health-related quality of life questionnaire (EQ-5D-5L) data collected from the optional online link, where available. Compliance with conveyance guidelines will be recorded and also, as part of the safety monitoring for the trial, ambulance attendance for any reason within 3 months of index presentation will be reported and monitored.

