### Formation of ambulance station clusters and randomisation

Ambulance station clusters will be formed from the 93 SWASFT ambulance stations in existence at the time of study set-up. Recent historical data on activity and general conveyance rates for all stations were collected to inform the formation of trial clusters and sample size calculations. After merging very small and closely located stations, while maintaining the largest possible number of similar sized clusters, 80 (mostly single station) ambulance station clusters were identified. Clinicians working from these stations use equipment bags strictly belonging to and stocked by that station.

The stepped wedge trial design is comprised of five stages, with each stage lasting 4 months. In the first stage, none of the station clusters will have access to the VAD and patients will be treated as per standard practice. The clusters will then be randomly allocated, by computer-generated sequences (stratified by location and balanced on cluster size), to include VADs with their equipment bags, in one of the four remaining stages, so that 20 clusters and their clinicians receive access to the VAD for the first time at each stage. Randomisation will be performed by an independent statistician otherwise unconnected with the trial.

Once the VAD has been introduced, the cluster will retain the use of devices for the remainder of the study so that by the fifth stage, all 80 clusters and their clinicians will have access to the VAD (see figure 2). Devices will be added to a clearly marked ‘Valsalva pouch’ attached to the standard equipment bag. These bags are checked and restocked daily and carried by all treating ambulances. All station clusters randomised to VAD use will initiate availability of the VAD on the same day, coordinated by SWASFT supply logistics and the local ambulance station ‘champions’ (listed as trial collaborators). These processes will be overseen by the Clinical Trials Unit to ensure protocol compliance as far as possible. Ambulance stations will be notified of activation with sufficient time to enable Valsalva pouches to be changed and all station clinicians to be notified. No other individuals outside the Lead Research Paramedic, logistics supply chain and the station clinicians will be made aware of the randomisation.

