### Determination of sample size

The sample size was calculated using formulae presented by Hussey and Hughes.^17^ Assuming a baseline non-conveyance rate of 10% (from routine and feasibility study data)^8^ and a 10% point increase in non-conveyance with VAD, an intracluster correlation coefficient of 0.01 and 90% power at the two-sided 5% level of significance, we estimated that the 80 ambulance clusters will need to recruit a total of 800 participants (without repeat presentations) to the trial. The intracluster correlation coefficient was estimated to be 0.009 for non-conveyance for all reasons (not just SVT) using routine data from 94 SWASFT ambulance stations for care episodes for the 12 months between 1 February 2019 and 31 January 2020, inclusive.

Each ambulance cluster would be expected to recruit two participants in each of the five stages (each stage lasts 4 months) over the 20 months of recruitment. The target effect size was based on the minimum clinically meaningful effect that would justify a change in practice, taking into account the benefits and cost of the devices while remaining plausible according to the feasibility trial data (12% absolute increase in non-conveyance (95% CI: 3 to 34)).^8^ Prior to commencement of the trial, we also undertook a data collection exercise, using the proposed trial eligibility and data collection methods. This showed 63 (95% CI: 50 to 77) eligible patients had undergone a VM for SVT in SWASFT over 1 month. This number was in keeping with data from our feasibility study and previous service evaluations and in excess of that needed in our sample size estimates (40/month). This will allow for repeat presentations (around 10% of all cases by the end of an SVT VM trial of similar duration) and opt-out of data use, which, from our patient and public involvement and engagement and feasibility work, we expect to be low.

Due to the study design, recruitment will also largely be determined by normal practice rather than specific trial activities. It was felt that 20 months to recruit 800 participants is conservative and achievable. However, initial study progress criteria are proposed to monitor the recruitment rate (see table 2).

**Table 2 T2:** Study progression criteria

Criteria	Green	Amber	Red
Individual-level recruitment	≥160 participants (100+%)	128–159 participants (80–99%)	<128 participants (below 80%)

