The use of routine data and delivery of the trial during normal care will contribute to study efficiency and help to ensure that study findings will be representative of real-life practice and improve external validity. Service-wide introduction of the intervention during normal practice, with assessment of the overall device use across the trust, will also give some measure of its acceptability and ease of implementation. This will also be useful to other ambulance trusts when considering the study findings.

The primary outcome of the study was carefully considered. Cardioversion was contemplated as an alternative primary outcome, but our feasibility study and other previous research have demonstrated challenges in providing robust evidence and timing of cardioversion. Conveyance is a clear, measurable outcome which is important to patients, clinicians and health services.

The study design means the trial recruitment rate will also be determined by normal practice. While this will ensure all eligible adult patients undergoing an SWASFT-delivered VM can be included in the trial, recruitment could potentially be affected by other factors affecting ambulance availability and wider pressures on the ambulance service. Previous feasibility work demonstrated a consistent incidence of VM treatment, at various time points, including during the COVID-19 pandemic. These data were used to determine the anticipated duration of the stepped wedge phases and overall trial duration. However, there is no certainty that the previously observed incidence rate will be maintained throughout this definitive trial. Recent, well-documented ambulance delays could affect recruitment rates if, for example, more patients make their own way to hospital.

The planned analysis of health-related quality of life (EQ-5D-5L) data through an optional questionnaire will be dependent on response rates to an invitation included in the PIL. Although it is known that response rates to health questionnaires are notoriously low in emergency settings,^20^ the main trial design and resources for the study do not allow for an alternative approach to collect these data. Recruitment and EQ-5D response rates will therefore be closely monitored and action considered in conjunction with the trial oversight committee, sponsor and funder, as required.

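### The 3-month outcome is meant to rule out postponed hospital attendance, but it sees only ambulance journeys and does not give the net effect on conveyance

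*Protocol article*

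**What the plan says.** All references are to the protocol article.

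- **Primary outcome:** conveyance at the index episode, taken from the ambulance service's electronic record. Under Data analysis, repeat presentations are left out of the primary analysis, so a participant left at home and conveyed later still counts as not conveyed.
- **Secondary outcomes:** later SVT call-outs over 3 months, with any conveyance that follows, are listed "to rule out the possibility that treatment postpones attendance to hospital". Ambulance attendance for any cause over the same period is also reported, as safety monitoring.
- **Follow-up data:** the Consent section describes the 3-month data as use of the ambulance service, and Study population and setting places the whole study within one service. No hospital or emergency department record is named as a follow-up source.
- **Discussion:** journeys without an ambulance appear once, as a way in which ambulance delays might lower recruitment: "if, for example, more patients make their own way to hospital".
- **Determination of sample size:** the target is "a 10% point increase in non-conveyance with VAD", with "an intracluster correlation coefficient of 0.01 and 90% power at the two-sided 5% level of significance". No 3-month event rate, precision target or margin is given for the postponement question.

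**The concern.** The stated purpose is about attendance at hospital, while the data are about attendance by an ambulance. Only participants not conveyed at index can have their attendance postponed, and if the VAD works there are more of them in the VAD condition. Journeys that the record misses would therefore tend to flatter the VAD.

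There is a second difficulty. The question is whether a fall in index conveyance is a real saving or partly a delay, and the answer needs index and later conveyance in the same participant. The two are listed as separate outcomes, and the later one is counted in everybody, including those who had already been to hospital. At stake is the claim in the Discussion that fewer conveyances would pay for the devices. If part of the fall were only delayed, the listed outcomes would not show directly how much remains.

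**Working it through.** **1. What the follow-up can see**

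| Route after non-conveyance at index | In the 3-month data? |
|---|---|
| Further call-out to this service, conveyed | Yes |
| Further call-out to this service, not conveyed | Yes, as an attendance |
| Hospital reached by any other route | No |

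Let *u* be the share of non-conveyed participants who later reach hospital unseen, taken as equal in both conditions. The documents give no value. With 10% (control) and 20% (VAD) not conveyed, the apparent gain is overstated by 0.20*u* − 0.10*u* = 0.10*u*. As *u* runs from 0 to 1, this runs from 0 to 10 points.

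**2. Who is counted in later conveyance**

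The roll-out gives 200 control and 200 VAD cluster-stages. At two participants each ("Each ambulance cluster would be expected to recruit two participants in each of the five stages") that is 400 per condition. Expected conveyed at index: 0.90 × 400 + 0.80 × 400 = 360 + 320 = 680 of 800. In these 680 a later conveyance is a new recurrence and not a postponed attendance. Postponement is possible in only 40 control and 80 VAD participants.

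**3. The plan's own sample size**

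Hussey and Hughes variance, with I = 80 clusters, T = 5 stages, U = 20(4+3+2+1) = 200, W = 20² + 40² + 60² + 80² = 12,000 and V = 20(16+9+4+1) = 600:

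Var = Iσ²(σ² + Tτ²) / [(IU − W)σ² + (U² + ITU − TW − IV)τ²]

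Here IU − W = 4,000 and U² + ITU − TW − IV = 12,000. With the control-rate variance 0.10 × 0.90 = 0.09 and ICC 0.01, τ² = 0.0009 and σ² = 0.0891/2 = 0.04455.

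- Var = 80 × 0.04455 × 0.04905 / (178.2 + 10.8) = 0.000925, so SE = 0.0304.
- Power = Φ(0.10/0.0304 − 1.96) = 90.8%. The N for 90% power is 777, or 800 at two per cell, which matches "the 80 ambulance clusters will need to recruit a total of 800 participants (without repeat presentations) to the trial".

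With the average of the two conditions' variances, power is 79.7%. That is a separate matter, but it is the right benchmark for step 5.

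**4. The 3-month outcome**

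The same formula is used with variance p(1 − p), where p is an assumed 3-month re-conveyance rate, and with ICC 0.01 carried over. The ICC matters little: at p = 10%, the SE is 0.0300 with ICC 0. The probability of excluding a rise of d when there is no postponement is Φ(d/SE − 1.96).

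| p (assumed) | SE | 95% half-width (points) | Exclude 10-point rise | Exclude 5-point rise |
|---|---|---|---|---|
| 2% | 0.0142 | 2.8 | >99% | 94% |
| 3% | 0.0173 | 3.4 | >99% | 82% |
| 5% | 0.0221 | 4.3 | 99.5% | 62% |
| 10% | 0.0304 | 6.0 | 91% | 38% |
| 15% | 0.0362 | 7.1 | 79% | 28% |

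Power to detect a true 5-point rise is 47% at p = 5% and 32% at p = 10%.

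**5. A combined outcome**

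The outcome is conveyance at index or within 3 months, with averaged variances and an assumed 5–10% of the control condition's non-conveyed participants conveyed later.

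- No extra postponement: never conveyed 9.0–9.5% against 18–19%, difference 9.0–9.5 points, power 75–77% (against 79.7% for index conveyance on the same footing).
- Half of the extra 10 points conveyed later: difference 5 points, power 33–34%.
- Across scenarios from no offset to full offset, the half-width is 5.7–6.9 points.

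**6. Follow-up across stage boundaries**

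The design has five stages, "with each stage lasting 4 months", and follow-up lasts 3 months. With uniform entry over a stage, 75% of participants in a cluster's last control stage have follow-up that passes the switch. The mean overlap is (3²/2)/4 = 1.125 months, or 1.125/3 = 37.5% of follow-up time. Last control stages are 80 of 200 control cluster-stages, so 0.40 × 0.375 = 15% of control follow-up time falls after the switch.

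**The case against.** The quoted purpose is an aside with no test, margin or decision rule attached. The article condenses a fuller protocol and defers to a statistical analysis plan that is not shown and may well define a combined outcome. Reporting index and later conveyance separately is normal practice. All of this stands, and for that reason the absence of a composite is not in itself an error. What remains is a purpose, stated in this document, that the data source named beside it cannot meet.

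Four stronger readings are tempting, and the documents do not support them.

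- *The plan expects non-conveyed participants to travel to hospital unaided.* It does not. The Discussion remark is hypothetical and concerns patients who never enter the trial.
- *The outcome is simply too imprecise.* No 3-month rate is documented. The only related figure, repeat presentations of about 10% of all cases over a similar trial, is not a 3-month re-conveyance rate. At assumed rates up to 10%, full cancellation of the target effect could usually be excluded for ambulance conveyance, and at 2–3% even a 5-point rise usually could be.
- *A null result will be reported as proof that there was no delay.* The article contains no such rule.
- *Follow-up that crosses a switch invalidates the comparison.* Analysis is by cluster status at the time of the VM, so attribution is defined, and 85% of control follow-up time precedes the switch. Exposure also needs a new attendance by a switched cluster. Censoring only the control follow-up would give the conditions unequal observation time in a binary outcome and could itself create an apparent excess under the VAD.

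The any-cause attendance measure and the unblinded review by an independent subgroup of the steering committee widen the monitoring. The attendance measure is still ambulance-based, and no hospital source is named for the review.

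**Conclusion.** The point holds in a limited form. The 3-month outcome can show a large rise in later ambulance conveyance. It cannot rule out postponed attendance at hospital, for two reasons that need no assumed rate: other routes to hospital are not recorded, and later conveyance is counted apart from index conveyance in a population expected to be 85% (680 of 800) already conveyed.

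On size, with an assumed rate of 5–10% and the primary outcome's ICC, the half-width is 4.3–6.0 points. A full 10-point offset would be excluded with 91–99.5% probability, and a 5-point offset with only 62–38%. These figures use a linear-scale approximation with equal cell sizes. The crossing of stage boundaries, about 15% of control follow-up time under uniform entry, deserves a note and no more. The change is worth making but does not threaten the primary analysis.

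**What to change.** 1. In Secondary outcomes, replace the rule-out purpose with 'to assess, for ambulance conveyance only'.
2. State as a limit that journeys to hospital made without this ambulance service are not seen, and that missing them would tend to favour the VAD.
3. Add a secondary outcome, 'conveyed for SVT at index or at any ambulance attendance within 3 months', analysed by VAD status at the index episode in the same mixed model and reported with its confidence interval. If the statistical analysis plan already defines it, a cross-reference is enough.
4. Note that about 15% of control follow-up time is expected to fall after the cluster's switch, assuming uniform entry. No control-only censoring analysis is advised.

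The cost is some wording and one extra analysis of data already collected. The combined outcome measures the net effect directly but brings no gain in precision and still misses non-ambulance journeys. The trial would have to make a more modest claim about postponement.

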### Other measures

Confirmation of the Valsalva strain method used will be recorded. Demographic data, including ethnicity, will also be extracted from the ePCR to describe the extent to which the two groups (intervention vs control) are similar with respect to patient characteristics and that all patient groups, commensurate with the local population demographic, have the opportunity to take part in the research.

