### Study population and setting

Eligible patients presenting to SWASFT with suspected SVT and who are treated with a VM by an SWASFT ambulance clinician, will be included. The study will be conducted entirely within SWASFT, UK. This ambulance service uses a searchable electronic patient care record (ePCR) as standard when attending patients. This was shown to be a reliable and easily searchable data source in our feasibility study. SWASFT also has an established clinical guideline advocating the use of an mVM and non-conveyance of successfully treated SVT patients.

The study aims to include all adult patients aged 18 years and over for whom there is a record of a VM delivered by an ambulance clinician, working out of a participating ambulance station, for presumed SVT.

Patients who subsequently withdraw consent for use of their data or have an existing general opt-out for use of routine National Health Service (NHS) data for research will be excluded from the trial. Data from patients who are prisoners at the time of treatment, patients with permanent lack of capacity as recorded by the treating clinician and patients solely treated by an SWASFT member of staff outside of the included ambulance station clusters (eg, air ambulance, Hazardous Area Response Team, British Association for Immediate Care doctor) will also be excluded. Data from patients previously included in the study will be excluded from the primary outcome analysis but will be used in analyses of some secondary outcomes. A summary table of the trial eligibility criteria is shown in table 1.

**Table 1 T1:** Trial inclusion and exclusion criteria

Inclusion criteria	Adult patients (age 18 years or over). Record of a Valsalva manoeuvre for presumed SVT having been delivered by an ambulance clinician assigned to a participating ambulance station cluster.

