### Study procedures

Potential study participants will undergo standard clinical assessment by ambulance clinicians. For suspected SVT this typically includes medical history, recording of routine initial observations of pulse, blood pressure, respiratory rate, oxygen saturation and the recording of a 12-lead ECG. Routinely collected clinical data are entered into the ePCR system and so are available for subsequent trial data extraction for eligible participants.

The screening of eligibility for VM treatment, the conduct of the VM and all other aspects of clinical care will be entirely governed by SWASFT clinical guidelines, interpreted and followed at the discretion of the treating clinician. On commencement of the intervention phase of the trial, SWASFT clinical guidelines will be updated to include the use of the VAD, where available as part of standard care.

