### Data analysis

Analysis will be conducted according to a prespecified statistical analysis plan written by the trial statisticians, approved by an independent statistician on the TSC and made publicly available ahead of database lock.

Participant and cluster (ambulance stations) characteristics will be summarised using means and SD or medians and IQRs for continuous variables and numbers and percentages for categorical variables, by condition status (intervention vs control) and overall.

In the main analyses, outcomes will be analysed using the intention-to-treat principle, based on intervention status of the cluster at the time of the VM, irrespective of whether there was evidence of device use. Per-protocol analyses will also be undertaken. Repeat presentations of patients previously recruited will be excluded from the primary analyses but included in secondary analyses. The intervention effect will be estimated through fitting mixed effects (‘multilevel’) regression models that allow for the correlation between outcomes of patients from the same cluster (station). The models will include fixed effects for the intervention effect and time (stage) and a random effect for the cluster.

Given the nature of the primary outcome and normally well-recorded routine data to be used in the trial, it is not anticipated that there will be a significant quantity of missing data. The trial Research Paramedic will make every attempt to retrieve any missing data. Should any key outcome data remain missing, sensitivity analyses may be proposed, using a range of assumptions where necessary and consideration given to suitable imputation.

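### The stated model has no patient covariate, so it forgoes a modest gain in precision and cannot adjust for a within-stage case-mix shift tied to device availability

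*Protocol article*

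**What the plan says.** On the model, the protocol article's Data analysis section states: "The models will include fixed effects for the intervention effect and time (stage) and a random effect for the cluster". No patient characteristic is named. The same section says that participant characteristics will be summarised by condition, and that analysis follows a prespecified statistical analysis plan to be made public before database lock.

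On patient characteristics, the Other measures section states: "Demographic data, including ethnicity, will also be extracted from the ePCR to describe the extent to which the two groups" are similar, and adds the aim of showing that all patient groups could take part. Both purposes are descriptive.

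On other data available before treatment, Study procedures says that assessment for suspected SVT typically includes "recording of routine initial observations of pulse, blood pressure, respiratory rate, oxygen saturation" and a 12-lead ECG. It says that routinely collected clinical data are held in the electronic record and can be extracted.

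On entry to the trial, Study population and setting includes adults "for whom there is a record of a VM delivered by an ambulance clinician" working from a participating station. Study procedures leaves clinical care, including who is suitable for the manoeuvre, to service guidelines applied at the treating clinician's discretion. The section on clusters and randomisation says that station clinicians are told when their station is activated.

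**The concern.** Clusters are randomised, but participants are identified afterwards by staff who know whether the device is on board. Randomising clusters does not protect against selection that the intervention itself causes. If the device makes clinicians readier to attempt a manoeuvre, or directs attempts to different patients, device-period and control-period patients in the same stage may differ in their baseline chance of conveyance.

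The article shows that there is room for this. The Introduction puts SVT attendances at about 800 a year, by comparison with another service and from audit data, and those treated with a manoeuvre at about 500. The progress criteria section recognises cases in which a manoeuvre was indicated but not done.

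Two things are at stake. Any such shift would sit inside the estimated treatment effect. Separately, a model that leaves out prognostic pre-treatment values gives up whatever precision they would bring.

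**Working it through.** **1. Inputs from the article.** "Assuming a baseline non-conveyance rate of 10"%; "a 10% point increase in non-conveyance with VAD, an intracluster correlation coefficient of 0.01"; "90% power at the two-sided 5% level of significance". There are 80 clusters (I = 80), 20 crossing over at each of four steps, five stages (T = 5) and two participants per cluster per stage (n = 2), so 800 in total. The method is that of Hussey and Hughes.

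**2. Formula.** With treatment indicators X:

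Var = I·σ²(σ² + Tτ²) / [(IU − W)σ² + (U² + ITU − TW − IV)τ²]

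- U = 20 × (4+3+2+1) = 200
- W = 20² + 40² + 60² + 80² = 12,000
- V = 20 × (16+9+4+1) = 600
- IU − W = 16,000 − 12,000 = 4,000
- U² + ITU − TW − IV = 40,000 + 80,000 − 60,000 − 48,000 = 12,000

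For total outcome variance v and ICC 0.01, τ² = 0.01v and σ² = 0.99v/2.

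**3. The plan's own figure.** Take v = 0.10 × 0.90 = 0.09. Then σ² = 0.04455 and τ² = 0.0009.

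- Var = 80 × 0.04455 × (0.04455 + 0.0045) / (178.2 + 10.8) = 0.000925, so SE = 0.0304.
- Power = Φ(0.10/0.0304 − 1.96) = 90.8%, and 777 participants give 90%.
- Treating 0.09 as the individual-level variance instead gives 90.5% and 785.

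The stated 800 is therefore reproduced with the control-rate variance in both conditions. With variance averaged over the two rates, v = (0.09 + 0.16)/2 = 0.125, SE = 0.0358 and power = 79.7%.

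**4. Adding covariates.** Let covariates explain a share R² of individual variance. Replace σ² by σ²(1 − R²) and leave τ² unchanged. The article gives no R², so the range is an assumption.

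| Assumed R² | Power, v = 0.09 | N for 90% | Power, v = 0.125 | N for 90% |
|---|---|---|---|---|
| 0 | 90.8% | 777 | 79.7% | 1,094 |
| 0.02 | 91.3% | 762 | 80.4% | 1,072 |
| 0.05 | 92.1% | 738 | 81.6% | 1,039 |
| 0.10 | 93.3% | 700 | 83.5% | 984 |

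At v = 0.09 the SE falls by 2.4% at R² = 0.05 and by 5.0% at R² = 0.10. The scaling is for a linear model. In a logistic mixed model, adjustment changes the odds ratio to one conditional on the covariates, so a standardised risk difference is the comparable summary.

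**5. Case mix.** Approximate bias = (risk difference between covariate levels) × (within-stage imbalance in that covariate). Purely as illustration, 0.20 × 0.05 = 1 percentage point and 0.30 × 0.10 = 3 points, against a 10-point target. The article supplies neither factor, and the direction could be either way.

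**The case against.** The strongest reply is that a covariate list belongs in the analysis plan. The article defers to such a plan, and saying what the models will include does not say that nothing else will be added. That stands. A reader might infer that characteristics are used only descriptively and that adjustment is ruled out, but the article says neither. The point is an improvement to the model as stated, not proof of an omission.

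The second reply is that much of the case-mix risk is already handled. The stage term takes out change common to all stations, the cluster effect allows for stable station differences, and allocation is stratified by location and balanced on cluster size. In addition, an assessor blind to allocation will classify the available, interpretable pre-manoeuvre ECGs as eligible or not. This also stands, but none of it adjusts for a within-stage shift linked to device status. The ECG review could reveal a change in the rhythms treated; as described, it does not enter the model.

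Third, adjustment is an incomplete remedy. Selection works through clinical judgement, and three covariates capture only part of it. A reader might take adjustment to cure the selection problem; it does not.

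Fourth, the data are less complete than one might assume. Observations are described as typical rather than universal, and pulse is available for extraction rather than stated to be in the trial extract.

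**Conclusion.** The point holds as a low-cost improvement of minor severity. The stated model has no patient covariate, the stated uses of the demographic data are descriptive, and the design leaves open a within-stage shift that the stage and cluster terms cannot remove.

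The precision gain is modest: about 1.3 to 2.5 power points (90.8% to 92.1-93.3%) with variance 0.09, or about 1.9 to 3.8 points (79.7% to 81.6-83.5%) with variance 0.125. Both ranges rest on an assumed R² of 0.05 to 0.10. Weakly prognostic demographics alone might bring less.

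Two stronger readings are not supported. One is that the trial has only about 80% power on its own inputs. That figure needs the averaged variance, whereas the control-rate variance reproduces the stated 90%; which variance is appropriate is a separate sample-size question. The other is that a definite part of the 10-point target is case mix. No figure in the article allows that bias to be sized.

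**What to change.** Prespecify age, sex and pre-manoeuvre heart rate as fixed effects in the primary model, and keep the stage and cluster terms. Report the effect as a risk difference standardised over the trial population. Keep the model without covariates as a named sensitivity analysis, and state that adjustment addresses measured case mix only.

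Age and sex should come with the demographic data already planned for extraction; the article names only ethnicity, so confirm this. Heart rate is in the electronic record but would have to be added to the extract. The cost is analysis wording, one added data field and a rule for a few missing covariate values, such as simple imputation. The change should be made before the analysis plan is signed off, while the statisticians are still blinded, so that the choice of covariates cannot be thought data-driven. If the analysis plan already contains such adjustment, nothing further is needed.
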